## Discussion

PDS impacts patients’ QoL and causes a financial burden for society. This large trial will evaluate the efficacy of acupuncture versus sham acupuncture in improving the symptoms of PDS.

This trial meets the methodological demand of adequate randomization and allocation concealment, blinding of patients, outcome assessors, and statisticians. A suitable control group is critical for a well-designed clinical trial. On the basis of literature review, superficial insertion at non-acupoints is the most commonly used approach for administering sham treatments among acupuncture trials [26]. Additionally, the amount of acupuncture is intensive, which is similar to clinical practice in China. Needles will be stimulated manually for at least 30 s at each acupoint and retained in place for 20 min. The treatment frequency is three sessions weekly.

The limitation of our trial is recall bias of pre-treatment symptom severity at the assessment of overall OTE. However, OTE is a reliable and frequently used outcome [27], which has been used as the primary outcomes in several trials [28–30]. Second, the acupuncturists are not blinded for the nature of intervention. Moreover, the use of a fixed block randomization may lead to block size exposure, which may not prevent selection bias from the prediction of treatment allocation in patients. At the end of this trial, we hope the results will provide more reliable evidence and clarify the value of acupuncture as a treatment for PDS.

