### Randomization and allocation concealment

All eligible patients will be randomly assigned to the acupuncture group or sham acupuncture group in a 1:1 ratio with a central web-based randomization (Beijing Guide Technology Co., Ltd.). The blocked randomization sequence will be computer-generated with the SAS 9.3 software by a professional statistician, who is not involved in the implementation and statistical analysis of the trial. The clinical research coordinator will be responsible for enrolling patients, obtaining informed consent and requesting randomization.

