### Masking

Due to the nature of acupuncture, masking of acupuncturists is quite difficult to achieve. Patients, outcome assessors, and statisticians who perform the statistical analyses will be blinded to group assignment. Participant’s allocated intervention will be not revealed until the statistical analysis is completed.

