### Trial status

This trial is currently recruiting patients.

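### Fixed blocks with unmasked acupuncturists leave a conceded route to predicted allocation; varying the block size for remaining patients would narrow it cheaply

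*Protocol article*

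**What the plan says.** - **Sequence and release** (Randomization and allocation concealment): "The blocked randomization sequence will be computer-generated with the SAS 9.3 software by a professional statistician". This statistician takes no part in conducting or analysing the trial. Patients are allocated "in a 1:1 ratio with a central web-based randomization". A clinical research coordinator enrols, takes consent and requests randomisation.
- **Masking**: "masking of acupuncturists is quite difficult to achieve". Patients, outcome assessors and the analysing statisticians are listed as blinded. The coordinator is not on that list.
- **Discussion**: "This trial meets the methodological demand of adequate randomization and allocation concealment". Among the limitations, the same section says "the use of a fixed block randomization may lead to block size exposure, which may not prevent selection bias from the prediction of treatment allocation".
- **Trial status**: "This trial is currently recruiting patients".

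The article gives no block size and does not say whether the list is shared or held by centre. It describes no step against the risk that it concedes.

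**The concern.** Acupuncturists know the arm of each patient they treat, so past assignments are known to people at the sites. When all blocks have one size and that size becomes known, someone who tracks past assignments can sometimes deduce the next one. If that knowledge reaches the person who enrols, the decision to approach, include or delay a patient can depend on the coming arm.

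That bias arises before randomisation, so blinding patients and assessors does not repair it. Adjustment for measured baseline severity can help with measured imbalance but not with unmeasured imbalance. Entry rests on reported symptoms, which leaves some room for judgement at enrolment.

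The Discussion also claims adequate concealment and concedes possible prediction. The second statement qualifies the first, but the article does not reconcile them.

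**Working it through.** The article gives no figure for predictability, so there is none to reproduce. Block size B is an assumption, shown for 4, 6 and 8.

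**Inputs from the article:** 1:1 allocation, fixed blocks, five hospitals, 280 patients.

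**Case A: B known, every earlier allocation in the block seen.** An allocation is certain once all B/2 places of one arm are used. The expected share of such allocations is 2/(B+2). Best-guess accuracy comes from exact enumeration. For B = 4, the chances of a right guess at positions 1 to 4 are 1/2, 2/3, 2/3 and 1, and (0.5 + 0.667 + 0.667 + 1)/4 = 0.708.

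| B | Certain in advance | If applied to all 280 | Best guess right |
|---|---|---|---|
| 4 | 2/6 = 33% | 93 | 70.8% |
| 6 | 2/8 = 25% | 70 | 68.3% |
| 8 | 2/10 = 20% | 56 | 66.6% |

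Chance alone gives 50% right guesses.

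**Case B: one list shared over five hospitals, only own-site allocations seen.** Further assumptions: equal recruitment, and block size and boundaries known. Certainty now requires that all B/2 used places of one arm fell at the observer's own site, so the share is 2/(B+2) × (1/5)^(B/2).

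| B | Certain in advance | Best guess right |
|---|---|---|
| 4 | 0.333 × 0.04 = 1.3% | 54.4% |
| 6 | 0.25 × 0.008 = 0.2% | 54.0% |
| 8 | 0.20 × 0.0016 = 0.03% | 53.7% |

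**Case C: blocks of 4, 6 and 8 mixed at random with equal probability, all earlier allocations seen, the set of sizes known.** Simulation of 100,000 allocations gives 2.4% certain and 67.9% of best guesses right. A repeat with 300,000 gives 2.3% and 68.1%.

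**Reading across.** Against Case A, mixing removes most of the certain predictions (from 20–33% to about 2%). Best-guess accuracy hardly moves: it falls from 70.8% against a fixed block of 4, and is slightly above the 66.6% for a fixed block of 8. Case C with a list at each centre is more predictable than Case B with a shared list (about 68% against about 54% right). Moving from a shared list to lists by centre could therefore make matters worse.

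**The case against.** The strongest reply is that this is a disclosed limitation of a recognised method, and that the article shows no working route to bias. Release is central, so the next assignment is hidden. The list is made by someone outside the trial's conduct, and the enroller is not the unmasked acupuncturist. Prediction needs the block size to leak, past allocations to reach the coordinator, block boundaries to be known, and enough of the sequence to be visible at one site. The article states none of these as fact, and may leave block size, stratification and staff access to the full protocol.

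Much of this stands. A reader might infer that up to a third of allocations are known in advance, or that enrolment is already biased. The documents support neither: one third is the upper case for B = 4, and a shared list brings the share to about 1% or less. A reader might also infer that the coordinator sees allocations because the masking list omits that role. The omission does not say so, and enrolling and requesting randomisation in one role is not itself a fault.

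What does not stand is that disclosure settles the matter. The article names the fixed block and its consequence itself, describes no countermeasure, and is still recruiting. The finding does not rest on the unstated block size.

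**Conclusion.** The point holds as an inexpensive improvement to the design, not as evidence of bias. Certain allocations could range from about 0.03% (B = 8, shared list) to 33% (B = 4, all earlier allocations in the block seen). The upper end assumes that the block size is known and that past allocations reach the person who enrols. The lower end assumes five equally recruiting hospitals on one list.

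A reader might infer that varying block sizes would make the problem disappear, so that the limitation could be deleted. That is not supported. Best-guess accuracy stays near 68% when all earlier allocations are seen, and patients already randomised in fixed blocks remain in the intent-to-treat population. The sample size is unaffected.

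**What to change.** 1. Confirm whether the present list is shared or by centre, and keep that structure.
2. For patients not yet randomised, have the independent statistician load a list with randomly varying block sizes (for example 4, 6 and 8) in the existing web system.
3. Withhold the block sizes and past allocations from the coordinator who enrols. This matters as much as the new list, because varying sizes alone leave best guesses nearly as good.
4. Keep the limitation, reworded to say that earlier patients were allocated in fixed blocks and later ones in varying blocks. Qualify the claim of adequate allocation concealment to match.

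The cost is a regenerated list and a short amendment during recruitment, with no extra patients.

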### Trial status

This trial is currently recruiting patients.

## Abbreviations

DSMB: Data and Safety Monitoring Board
eCRF: Electronic case report form
EPS: Epigastric pain syndrome
FD: Functional dyspepsia
HADS: Hospital Anxiety Depression Scale
ITT: Intent-to-treat
NDI: Nepean Dyspepsia Index
OTE: Overall treatment effect
PDS: Postprandial distress syndrome
PP: Per-protocol
QoL: Quality of life
